**Methods and analysis:**

This research will estimate the impact of neighbourhood GBS access, GBS exposure and visits to GBS on the risk of common mental health conditions and the opportunity for promoting subjective well-being (SWB); both key priorities for public health. We will use a Geographic Information System (GIS) to create quarterly household GBS accessibility indices and GBS exposure using digital map and satellite data for 1.4 million homes in Wales, UK (2008–2018). We will link the GBS accessibility indices and GBS exposures to individual-level mental health outcomes for 1.7 million people with general practitioner (GP) data and data from the National Survey for Wales (n=~12 000) on well-being in the Secure Anonymised Information Linkage (SAIL) Databank. We will examine if these associations are modified by multiple sociophysical variables, migration and socioeconomic disadvantage. Subgroup analyses will examine associations by different types of GBS. This longitudinal study will be augmented by cross-sectional research using survey data on self-reported visits to GBS and SWB.

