**Figure 1 F1:**
[figure not shown]
Residential GBS access for each home. (1) Network buffer defines household access boundary (eg, 10 min walk). (2) GBS A and B included in access estimates including access points, rights of way and facilities such as benches (GBS C excluded). (3) Access measures include GBS quality, size, function and weighted network distances (d_i_) to access points. (4) Longitudinal exposure estimates created through quarterly repeat analysis. (5) GBS, green-blue spaces.

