### GBS accessibility and exposure dataset

There is no clear consensus in the existing literature on the most appropriate measures of GBS access and/or exposure.^42^ Using the aforementioned environment datasets, this project will collate a set of measures using criteria including longitudinal consistency, spatial resolution and evidence for associations with mental health and SWB outcomes. We will create residential-level exposure measures by modelling the ambient home environment, that is, the GBS immediately surrounding their home and what they see out of their window. This metric will include measures such as greenness (NDVI), urban trees and garden size. The access measures will represent people’s potential to visit GBS in their locality. We will adapt a previous methodology that modelled ‘change in alcohol outlet density and alcohol-related harm to population health’ (CHALICE).^60^ The distance decay for this accessibility model will be updated to emulate how people engage with GBS as opposed to alcohol outlets. People will behave differently in accessing GBS, compared with how they may access alcohol outlets. For example, people may be prepared to walk or drive further to access some green blue spaces compared with alcohol outlets.^61^ Our modelling will consider differential associations for key subgroups (eg, deprived populations) thereby minimising risks that recommendations could increase inequalities. We will create a number of accessibility and exposure measures, allowing planners to consider the configuration (size, function, quality) of the most beneficial mix of spaces. We will also measure, for each adult, change in GBS access and exposure for the study period. Again, we will build on the CHALICE study^62^ that measured change in alcohol outlet density by calculating change in density between the current and previous quarter and also the change between each quarter and baseline.

The longitudinal, household-level, GBS accessibility and exposure dataset will be imported into the SAIL databank and linked with health datasets that are held within the SAIL Databank. Household identifiers (Unique Property Reference Numbers, UPRNs) will be used to distinguish each household in the GIS and will have attached to each a GBS accessibility and exposure index (see figure 3). Household identifiers will be replaced with a Residential Anonymised Linking Field within SAIL.^63^

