## Statistical analysis

### Outcome variables

#### WP1 and 2: primary outcome - CMD

Change in counts of CMD treatments for adults identified as CMD cases within the corresponding time periods for the 70% of adults in Wales for whom we have GP data records in SAIL (1.7M adults). Prevalence algorithms,^65 66^ detect cases of CMD (anxiety and depression) from routinely collected GP data. We will use the algorithm that incorporates: an historical diagnosis and currently treated, with current diagnosis whether treated or untreated, to identify CMD cases. For each adult, and for the time periods (quarters) identified as a CMD case, treatments will be counted per day and aggregated into quarterly counts. Figure 4 shows a conceptual model of exposure variable (GBS access and exposure) and primary outcome variable (CMD treatments).

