#### WP1: secondary outcome - GP events

We have the total number of events recorded for each person in a WLGP dataset. We will calculate the number of GP events, converting to a binary daily activity or no activity aggregated to quarterly counts. This eliminates double counting (eg, counting the return of large quantities of test results only once). These are purposefully all events rather than those related only to CMD because this will capture people who frequently visit their GP but for whom no CMD diagnosis has been made. This will allow us to explore social isolation and as indicator of undiagnosed CMD.

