### Analysis plan

We will provide descriptive statistics of GBS access and exposure and changes in GBS access and exposure by household, Lower Layer Super Output Area (LSOA), deprivation quintiles using Welsh Index of Multiple Deprivation (WIMD) and population characteristics. NSW data will have descriptive statistics of each of the survey questions we will use (number of visits, labour market status, etc).

Across both WPs, we have outcomes of two distinct types: continuous (SWB) and counts (CMD treatments and GP event days). We intend to analyse the continuous outcome using a linear model. Poisson models will be used to analyse the longitudinal count data.

Our data are hierarchical in nature: WP1: three-level data: LSOA/Individual/Time (Quarter); WP2: two-level data: LSOA/Individual. Accordingly, we will adopt a multilevel modelling approach. We will generalise the standard linear and Poisson models to handle two or three levels of variation, as appropriate. The resulting two-level and three-level models will allow us to estimate the extent to which variation at each level may be explained by confounding variables (see table 2). Having controlled for confounders, we will proceed to add access and exposure variables to our models, thereby allowing us to test for the significance of the access and exposure variables in the presence of the confounders. Inclusion of these variables in the above models will permit us to estimate their direct effects on our outcomes. Having included the main effects of both confounders and access and exposure variables, we will proceed to test for the significance of selected pairwise interactions of interest, as shown in table 2.

**Table 2 T2:** Analysis summary (P: primary; S: secondary)

WP	Outcomes (type)	Exposures	Confounders	Interactions of interest
1	P: CMD (count)	P: Access and exposure to GBS.	LSOA level: Quintile of deprivation (WIMD). Category of urban/rural settlement type (ONS classification).	Change in access and exposure to GBS by deprivation.
	S: GP event days (count)	S: Time of move(s).	Individual level (SAIL): gender, age, comorbidities.	Change in access and exposure to GBS by time of move(s).
2	P2: SWB (continuous)	P2: Access and exposure to GBS.	LSOA level: as per WP1.	Exact number of visits by individual level deprivation.

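### WP1 relates quarterly counts to quarterly GBS exposure, including satellite greenness, with no season or calendar-year term among its stated confounders, so shared calendar effects can be read as effects of GBS

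*Protocol article*

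**What the plan says.** **Exposure.** The abstract (Methods and analysis) plans to "create quarterly household GBS accessibility indices and GBS exposure using digital map and satellite data for 1.4 million homes in Wales" for 2008–2018. The Figure 1 legend, on residential access, adds: "Longitudinal exposure estimates created through quarterly repeat analysis". On the ambient exposure, the section GBS accessibility and exposure dataset states: "This metric will include measures such as greenness (NDVI), urban trees and garden size". The same section says that change in access and in exposure will be measured for each adult. It builds on an earlier alcohol-outlet study that worked by "calculating change in density between the current and previous quarter and also the change between each quarter and baseline".

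**Outcomes.** Both WP1 outcomes are on the same time grid. For the primary outcome, "treatments will be counted per day and aggregated into quarterly counts". GP events are handled by "converting to a binary daily activity or no activity aggregated to quarterly counts".

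**Model.** The Analysis plan specifies multilevel Poisson models with three levels: LSOA, individual and quarter. Confounders enter first, by reference to Table 2. Access and exposure variables are then added and tested. For WP1, Table 2 lists "LSOA level: Quintile of deprivation (WIMD). Category of urban/rural settlement type (ONS classification" at area level and "Individual level (SAIL): gender, age, comorbidities" at person level. Timing of house moves is there as a secondary exposure. No season, quarter-of-year, calendar-year or trend term appears in the article.

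**The concern.** Exposure and outcome are both followed quarter by quarter for 11 years, and nothing in the stated adjustment set represents calendar time. Greenness measured by NDVI has a yearly cycle; the outlet density for which the change metric was devised has none of that kind. The article says the distance decay will be adapted to GBS but does not say the same of the quarterly lag.

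Anything that moves the outcome for the whole population at once, such as a winter rise in consultations or a long-term rise in prescribing, can therefore load onto whatever exposure moves at the same time. The Discussion states a causal aim, namely whether improved GBS lowers CMD risk, and intends the results for planning policy. If treatments happen to fall in the greener quarters, the false signal is protective, which is the direction the study hopes to find. A larger cohort does not cure this: the bias stays and the interval around it shrinks.

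**Working it through.** The article gives no effect size, power or error rate on this point, so there is no figure of its own to reproduce.

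**Step 1: what the stated model can absorb.** For person i in quarter t, log rate = confounders + β·x(it) + area effect + person effect. Suppose β = 0 but the true log rate contains a term s(t) shared by everyone. Area and person effects are constant over time, and an occasion-level term is independent between people, so neither removes s(t). Deprivation, urban/rural category, gender and comorbidities do not follow the calendar. Age, if updated each quarter, can take up part of a linear trend but no season. What remains of s(t) goes to β in so far as x follows the same calendar.

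**Step 2: approximate size.** All values here are assumptions. Unit of x: 0.1 NDVI. Seasonal pattern over the four quarters: −1, 0, +1, 0 (variance 0.5). NDVI swing ±0.10 = ±1 unit; residual SD 0.04 = 0.4 unit (variance 0.16). The outcome log rate moves by −a times the pattern. Within-person slope ≈ cov(x, s)/var(x).

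- NDVI level: −a × 0.5/(0.5 + 0.16). For a = 0.05: −0.0379, RR 0.963. For a = 0.02: −0.0152, RR 0.985.
- Quarter-to-quarter change: its pattern is −1, +1, +1, −1 (variance 1), its noise variance is 2 × 0.16 = 0.32, and its covariance with the season is 0.5. Slope = −a × 0.5/1.32. For a = 0.05: −0.0189, RR 0.981. For a = 0.02: −0.0076, RR 0.992.
- Trend only in the outcome (+3% per year), with NDVI rising 0.005 (0.05 unit) per year: time variance over 11 × 4 = 44 quarters is (44² − 1)/12/16 = 10.08 years². Slope = 0.05 × 0.03 × 10.08/(0.66 + 0.05² × 10.08) = 0.0151/0.685 = 0.0221, RR 1.022. Change from the previous quarter has a constant mean under a linear trend, so it takes none of this bias. Change from baseline differs from the level only by a constant within each person, so it takes the same within-person bias as the level.

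**Step 3: simulation of a random-intercept Poisson model.** True effect zero; 800 people, 44 quarters, 40 replicates per scenario; gamma-distributed person effect; mean 0.6 treatments per quarter; between-home NDVI SD 0.12; other values as in Step 2. The LSOA level, house moves and restriction to CMD-case quarters were left out. Entries are RR per 0.1 NDVI, with the proportion of replicates rejecting at the two-sided 5% level in brackets. Where two values are given, they are for age at baseline / age updated each quarter.

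| Scenario | Level, Table 2 terms | Level, + quarter-of-year and year | Quarterly change, Table 2 terms | Quarterly change, + quarter-of-year and year |
|---|---|---|---|---|
| Season ±5% | 0.9660 / 0.9656 (1.00 / 1.00) | 1.0007 (0.05) | 0.9814 (0.85) | 1.0012 (0.05) |
| Season ±2% | 0.9878 / 0.9873 (0.35 / 0.38) | 0.9997 (0.07) | 0.9939 (0.20) | 0.9989 (0.05) |
| Trend only | 1.0243 / 1.0120 (0.95 / 0.28) | 1.0005 (0.05) | 0.9994 (0.00) | 1.0006 (0.03) |
| Season ±5% and trend | 0.9900 / 0.9775 (0.28 / 0.88) | 0.9982 (0.00) | 0.9797 (0.97) | 1.0005 (0.03) |
| Neither | 0.9983 / 0.9978 (0.10 / 0.10) | 0.9989 (0.05) | 0.9998 (0.05) | 1.0022 (0.00) |

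With 40 replicates, the standard error of a 5% rejection rate is √(0.05 × 0.95/40) = 0.034, so 0.00–0.10 is compatible with the nominal level. Quarter-of-year alone is not enough when there is a trend: RR 1.0624 (trend only) and 1.0600 (both), rejected in every replicate.

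**Step 4: scale.** If all 1.7 million adults contributed in the same way, standard errors would be about √(1,700,000/800) = 46 times smaller than in the simulation. Fewer contribute to the CMD outcome, which is counted only in case quarters, but far smaller biases than these would still reach significance.

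**The case against.** Table 2 is a summary in a condensed article, and nothing calls it exhaustive. The strengths and limitations mention many potential confounders, and the coding of time in a longitudinal model is often left to an analysis plan, which is not shown here. Quarter is named as a level, and the text does not rule out quarter in the fixed part as well. NDVI is one of several example measures, the text does not say whether it is a quarterly or a yearly value, the Figure 1 legend concerns access, and the change definition describes the earlier study.

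Part of this stands. A reader might infer that the list is closed or that calendar terms are excluded; the article says neither. A reader might also infer that the quarter-to-quarter contrast is mainly season whatever the exposure. The documents do not support that: access built from map data, access points and network distance is hardly seasonal, and the Design section names house moves as a source of change. Nor does the text support saying that season and trend will be read as a GBS effect. That requires the outcomes to vary with the calendar, and the article gives no data on this. A yearly or season-matched NDVI would remove the seasonal part.

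It does not dispose of the point. The article names the confounders down to the settlement classification, and it sets the order in which exposure is tested after them. The only time grid it states for the exposure is quarterly. Followed as written, the model has no protection against shared calendar effects.

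**Conclusion.** The point holds in a conditional form. As stated, the WP1 model cannot separate GBS from calendar effects shared by everyone.

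- **Season** threatens NDVI-type exposure sampled quarterly, and its quarterly change. With the assumed ±0.10 NDVI swing and an outcome swing of 2–5%, the false RR is about 0.97–0.99 per 0.1 NDVI for the level and 0.98–0.99 for the quarterly change.
- **Secular trend** threatens exposure levels and change from baseline, including map-based access that drifts over the period. With the assumed trends in NDVI and outcome, the false RR for NDVI level is 1.02 with age at baseline and 1.01 with age updated. Trend alone hardly touches quarter-to-quarter change.

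These figures illustrate a mechanism and do not predict the study's bias. Every numerical input is assumed, and both direction and size depend on outcome patterns that the article does not report. The conclusion is confined to WP1; nothing in this working supports extending it to the cross-sectional WP2 models.

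**What to change.** 1. Add a fixed effect for each calendar quarter to every WP1 model and to the WP1 row of Table 2. Quarter-of-year plus calendar year is an acceptable shorter form; season without year is not enough.
2. Define change in NDVI against the same quarter of the previous year, or use an annual or deseasonalised NDVI. Keep the calendar-year terms in either case.
3. State whether age is fixed at baseline or updated each quarter, and do not rely on it to carry the time trend.

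Cost: at most 44 − 1 = 43 extra terms, or 3 + 10 = 13 in the shorter form, and a changed lag in one derived variable. Intervals will be somewhat wider, because variation shared by the whole population no longer counts as information on GBS. A year-on-year lag leaves the first four quarters without a change value, where the quarterly lag loses only the first, unless earlier greenness data are available. No new outcome data are needed.

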**Ethics and dissemination:**

All data will be anonymised and linked within the privacy protecting SAIL Databank. We will be using anonymised data and therefore we are exempt from National Research Ethics Committee (NREC). An Information Governance Review Panel (IGRP) application (Project ID: 0562) to link these data has been approved.

The research programme will be undertaken in close collaboration with public/patient involvement groups. A multistrategy programme of dissemination is planned with the academic community, policy-makers, practitioners and the public.

Strengths and limitations of this studyThis retrospective controlled evaluation of a natural experiment includes the majority of adults in Wales, UK between 2008 and 2018, minimising selection bias.Generating a national longitudinal dataset of changes in green-blue spaces (GBS) exposure and access to GBS for households will reduce ecological fallacy.Spatial and temporal accessibility data linked for individuals and their routinely captured health service use, together with potential confounders, will allow us to investigate the impact of GBS on well-being.Detailed self-report data on well-being and GBS visit behaviour from cross-sectional national survey data will be linked to health service utilisation data.Despite including a large number of potentially confounding variables, this non-randomised study using routinely recorded data may omit some unknown confounders, thereby introducing a moderate level of bias due to confounding.

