Many studies have found that access to GBS can vary across socioeconomic status (SES) areas; with more deprived areas tending to have poorer access to GBS.^24 25^ Differences in the distribution of GBS across SES may influence and contribute to SES-related health inequalities.^26^ Furthermore, individuals from higher SES groups are more likely to select living in greener neighbourhoods.^27^ Previous studies lack censoring for births, deaths and migration, which may have led to health selection effects which can alter the strength of association. There is also a lack of large-scale population-level studies which have systematically and explicitly examined associations within and between subgroups other than SES^10^ (eg, by gender,^28–30^ age, education^22 31^). Furthermore, ethnic minority groups are under-represented in studies due to selective non-response.^32^ Studies that have focused on differences between ethnic minorities found positive effects of GBS on well-being differed by ethnicity^33^ and ethnic minorities had poorer access to GBS.^34^

Study methods used to define access to GBS differ; some studies have calculated small area-level metrics and others have used distances. There is no accepted method to define GBS or for measuring different types of GBS (eg, according to general land cover categories, ecosystems or landscape classifications).^35–41^ However, it is difficult to expect an authoritative voice on defining GBS access because how people engage with GBS varies by population subgroup and environmental context. Therefore, how GBS is defined will vary by study design and the focus of the research. We propose to take an approach that will consider land use but also access points, rights of way and amenities such as benches. There are also differences in study aims because of differing perspectives; such as health research, environmental research and policy. Few studies have also considered the issue of access to blue spaces,^42 43^ which has also contributed to diversity in GBS accessibility measures. Although there is now a significant body of research, there are few longitudinal studies on mental health outcomes in response to changes in GBS access or with assessments of actual visits to GBS.^44–47^

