	P1: CMD (count)	S: Level of engagement in 150+ min of moderate or vigorous intensity activity per week.	Individual level and NSW: gender, age, comorbidities, highest educational qualification, marital status (incl. living with partner).	Exact number of visits by residential GBS.
			Exact number of visits made outdoors for recreation in last 4 weeks.	

CMD, common mental health disorder; GBS, green-blue spaces; GP, general practitioner; NSW, National Survey for Wales; ONS, Office for National Statistics; SAIL, Secure Anonymised Information Linkage; SWB, subjective well-being; WP1, work package 1.

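### WP1 adjusts for socioeconomic status only by area deprivation quintile, although the article itself names individual selection into greener areas and then calls the residual confounders unknown

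*Protocol article*

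**What the plan says.** **Selection mechanism.** The Introduction states that "individuals from higher SES groups are more likely to select living in greener neighbourhoods". It adds that unequal distribution of GBS may contribute to SES-related health inequalities.

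**WP1 adjustment (Analysis plan, Table 2).** At area level the entry is "LSOA level: Quintile of deprivation (WIMD", together with urban/rural settlement type. At person level it is "Individual level (SAIL): gender, age, comorbidities". Table 1 lists no individual socioeconomic field for the routine datasets.

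**Residual bias (strengths and limitations).** The study "may omit some unknown confounders, thereby introducing a moderate level of bias due to confounding".

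**WP2 (Table 2).** The exposures are again GBS access and exposure, and the CMD count is again an outcome. The added covariates are "highest educational qualification, marital status (incl. living with partner". One interaction of interest is "Exact number of visits by individual level deprivation". Labour market status is mentioned only among the survey descriptives: "number of visits, labour market status, etc". The Figure 3 legend says that CMD from GP records will be linked to survey respondents at individual level.

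**Use of WP2 to check WP1.** The article describes none for SES. The only related check is possible stratification by CMD, to look for reverse causation (Objectives, WP2).

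**The concern.** A factor that influences both where a person lives and that person's mental health treatment confounds the GBS estimate. The article names such a factor at the level of the individual, but WP1 handles it only with a five-category area measure. People within one quintile still differ in income, education and housing choice, and the choice of a greener street within a quintile is the selection that the Introduction describes.

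The Discussion gives WP1 a causal aim and intends the results for planning and policy. With 1.7 million adults the sampling error will be small, so even modest confounding could look like a clear protective effect. Describing the remaining confounders as unknown tells readers that nothing specific could be checked. The linked survey data would allow at least one specific check.

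**Working it through.** **1. Does the WP1 model remove individual SES?**

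- The Analysis plan describes a three-level Poisson model (area, individual, quarter). Access and exposure are added as main effects after the confounders. No split into within-person and between-person exposure is described, so the coefficient draws on both. The between-person part carries stable SES differences.
- The Design section counts moving home as a source of exposure change. SES selection acts through moves, so the within-person part is not fully protected either.
- Confounding by individual SES within quintile can therefore remain.

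**2. How large could it be?** The documents give no association of individual SES with GBS or with CMD treatment, so every input here is an assumption. For a binary low-SES factor with rate ratio RR, and low-SES prevalence p1 in greener and p0 in less green homes of the same quintile, a true null appears as

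[1 + p1(RR − 1)] / [1 + p0(RR − 1)]

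| RR | p1 | p0 | Calculation | Apparent rate ratio |
|---|---|---|---|---|
| 1.2 | 0.30 | 0.35 | 1.06 / 1.07 | 0.991 |
| 1.5 | 0.30 | 0.40 | 1.15 / 1.20 | 0.958 |
| 2.0 | 0.25 | 0.45 | 1.25 / 1.45 | 0.862 |

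For a continuous exposure, per SD of GBS, the bias in the log rate ratio is ln(RR) × r × 0.5. Here 0.5 is the SD of an even split and r is the residual correlation after the quintile. RR 1.3 with r 0.05 gives 0.0066, and RR 2.0 with r 0.10 gives 0.0347. The apparent rate ratios are 0.993 and 0.966. The two ranges differ because the contrasts and assumptions differ.

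**3. What sample could measure the shift?**

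- The article's own WP2 figure reproduces: 12 000 per year × 0.5 asked the visit questions × 2 years = 12 000.
- At 70% GP coverage, assumed to hold for respondents, 12 000 × 0.70 = 8 400.
- The check needs no visit data. If the education item is asked of all respondents, the base is 12 000 × 2 × 0.70 = 16 800.

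**4. Is the shift estimable there?** A simulation (300 runs per setting, overdispersed Poisson counts, 8 400 people, half in greener homes, no area clustering) fitted the GBS effect with and without SES.

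| Setting in step 2 | Mean shift in log rate ratio | SD of shift | SD of the adjusted GBS effect |
|---|---|---|---|
| Low | −0.009 | 0.004 | 0.063 |
| Middle | −0.042 | 0.008 | 0.065 |
| High | −0.148 | 0.017 | 0.070 |

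Both fits use the same people, so most of the sampling error cancels in the shift. With 16 800 people, the middle SD would be about 0.008 × √(8 400/16 800) = 0.006.

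**5. Comparison with WP1 sampling error.** Scaling 0.063 to 0.070 by √(8 400/1 700 000) = 0.070 gives about 0.004 to 0.005. This is a rough guide only. It ignores area clustering and repeated quarters, and it treats all 1.7 million as contributing, although treatments are counted in quarters when an adult is a CMD case. On the same greener/less green contrast, the assumed biases of 0.009 to 0.148 exceed it.

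**The case against.** Much of the case on the other side stands.

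- **The article is a condensed document, and a sensitivity analysis may sit in the full plan.** This is fair for the missing check taken alone. But the article itself fixes the WP1 covariates and labels the residual confounders unknown, which conflicts with its own Introduction.
- **The limitation is disclosed.** The box says "Despite including a large number of potentially confounding variables, this non-randomised study using routinely recorded data may omit some unknown confounders" and concedes a moderate bias. A reader might infer that the large number refers to the short WP1 list. It refers to the whole study, WP2 included, so it is not a misstatement about WP1. What remains is the word unknown.
- **WP1 is longitudinal.** It measures change from the previous quarter and from baseline, includes time of move(s) as an exposure, and tests interactions of change with deprivation and with time of move(s). Stable SES biases a change estimate less than a level estimate. This reduces the concern but does not remove it, for the reasons in step 1 of the working.
- **The sign is not established.** A reader might infer a known bias towards protection. The documents link SES to health inequalities only in general terms, and treatment counts also reflect care-seeking. The direction is probable only if low SES raises CMD treatment counts.
- **WP2 already plans an education-adjusted CMD estimate.** That is true. But with an SD of 0.06 to 0.07 in the simulation at 8 400 people, and a different sample and period, setting it against WP1 would not isolate SES. The paired with/without comparison is needed.
- **A survey-based correction may mislead.** WP2 is cross-sectional, and marital and labour market status may result from CMD. The proposed fix is limited accordingly.

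**Conclusion.** The point holds in a limited form. WP1 does adjust for SES, but only at area level. Individual selection, which the article names, can remain within quintile, and the article should not describe it as unknown.

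Its size cannot be derived from the documents. The illustrative rate ratios of 0.99 to 0.86 (greener against less green homes) and 0.993 to 0.966 (per SD) rest wholly on assumed inputs, and the low end is negligible.

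A reader might go further and conclude that a survey-corrected figure should replace the WP1 estimate or carry the policy conclusion alone. The documents do not support that. A shift seen in a 2016-18 cross-sectional survey estimates or bounds the bias in 2008-18 longitudinal estimates only if it carries over between the two settings. This is a change that should be made because it is cheap and informative; it does not invalidate the WP1 design.

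**What to change.** 1. In the strengths and limitations, name individual SES as a known confounder not held for WP1, in addition to any unknown ones.
2. In survey respondents with linked GP records, fit the planned WP2 CMD count model with the WP1 confounder set only, then add highest educational qualification. Use the same people in both fits.
3. Add marital and labour market status only as a further sensitivity step, because they may be consequences of CMD.
4. Report the shift in the GBS coefficient, with its uncertainty, as a pre-stated quantitative bias analysis beside the WP1 estimate.
5. State the assumption needed to carry a cross-sectional shift over to the longitudinal estimates, and state which base is used: about 8 400 (visit-question half-sample) or about 16 800 (education item asked of all), both at 70% coverage.

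**Cost.** One extra model in data already planned for linkage, and a more cautious WP1 conclusion.
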